## Laboratory procedures

All stool samples will be transferred to the HCLU on the day of collection, and will be examined by experienced laboratory technicians and the PhD-student. At the baseline screening, 2 Kato-Katz thick smears *(*41) from one stool sample per individual using 41.7 mg of stool will be prepared and examined quantitatively for the presence of hookworm eggs after a clearing time of 20-30 min, and subsequently for *A. lumbricoides* and *T. trichiura* eggs. The eggs of *A.* *lumbricoides*, hookworms and *T. trichiura* will be counted and recorded separately. From 250 randomly selected stool samples 1-2 g will be preserved in SAF for subsequent examination with the FLOTAC method *(*54).

From children included into the randomized controlled trial and thus providing another stool sample at the day of treatment and 2 consecutive stool samples for the follow up, a double Kato-Katz thick smear will be prepared and examined. At the days of follow up 1-2 g of stool, from those individuals examined with FLOTAC before treatment and who have been included in the trial, will again be preserved in SAF for subsequent examination with the FLOTAC method. All laboratory investigations will be blinded, e.g. the technicians examining the Kato-Katz slides or FLOTAC apparatus will not be aware of the treatment regimen of the participants. A random sample of 10% of the Kato-Katz thick smears will be re-examined by a Tanzanian senior laboratory technician for quality control.

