# Data analysis

The following data will be available for each individual:

Name

Age

Sex

Date of treatment

Drug used

Date of follow up

Parasitological data of first stool examination (double Kato-Katz thick smear)

Parasitological data of second stool examination (double Kato-Katz thick smear and single FLOTAC)

Parasitological data of follow up (2 stool samples with 2 Kato-Katz thick smears per sample and single FLOTAC)

Data on adverse events of treatment after 3 h (acute) and 72 h (solicited).

All data will be entered twice in Microsoft Excel version 10.0 (2002 ® Microsoft Corporation) by local staff in Zanzibar. Datasets will be compared using EpiData version 3.1 (EpiData Association; Odense, Denmark), and discrepancies removed based on the original records by the PhD student ([name]) when back in Switzerland. Statistical analyses will be carried out by the PhD student with JMP version 5.0.1 (SAS Institute; Cary, NC, United States of America). The CR of the treatments and the ERR will be compared for each drug according to the results of either the Kato-Katz or the FLOTAC method or the combination of both methods.

In addition, the frequency and severity of acute and solicited adverse events of the different drug regimens will be compared. The latter analysis will try to seek differential effects according to age, sex and initial parasite load.

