**Week 2 to 5**

- Collect filled stool containers from 1st 200 pupils and record them on the form

- Hand out labelled stool collection containers to 2nd 200 participants

- Transport collected full stool containers to the laboratory

- Prepare 2 Kato-Katz slides from each stool sample as described beyond

- Preserve 1 g of stool in SAF from ~250 randomly selected children

 Repeat the procedure until 500-600 children infected with *T. trichiura* are identified (approximately when stool samples of 2000 children are examined)

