**Week 9 and 10**

- Distribute labelled stool container to all children treated in the randomized trial

- Collect filled stool containers from all children and transport them to the laboratory, distribute a labelled new stool container for every one that was collected until each child submitted 2 stool samples after treatment

- Prepare 2 Kato-Katz smears from each stool sample and examine as described beyond until 2 consecutive stool samples from all children included into the trial were examined with the Kato-Katz method

- Preserve 1 g of 1 stool sample in a labelled container with 10ml SAF from the sub-sample of children randomly selected to be examined with FLOTAC and which finally entered the trial

- Inform participants in person about the parasitological diagnosis

- Treatment of all participating school-children free of charge with albendazole by members of the national helminth control team

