**Appendix 5: Overview participation**

| **ID** | **Name** | **Sex** | **Age** | **Sample A (No. K-K)** | **RCT**  **(Yes/No)** | **Sample B (No. K-K)** | **Sample A (FLOTAC)** | **Treatment**  **(Alb, Meb, Alb+Ivm, Meb+Ivm)** | **Sample C (No. K-K)** | **Sample D (No. K-K)** | **Sample C/D (FLOTAC)** |
| --- | --- | --- | --- | --- | --- | --- | --- | --- | --- | --- | --- |
| **0001** |  |  |  |  |  |  |  |  |  |  |  |
| **0002** |  |  |  |  |  |  |  |  |  |  |  |
| **0003** |  |  |  |  |  |  |  |  |  |  |  |
| **0004** |  |  |  |  |  |  |  |  |  |  |  |
| **0005** |  |  |  |  |  |  |  |  |  |  |  |
| **0006** |  |  |  |  |  |  |  |  |  |  |  |
| **0007** |  |  |  |  |  |  |  |  |  |  |  |
| **0008** |  |  |  |  |  |  |  |  |  |  |  |
| **0009** |  |  |  |  |  |  |  |  |  |  |  |
| **0010** |  |  |  |  |  |  |  |  |  |  |  |
| **0011** |  |  |  |  |  |  |  |  |  |  |  |

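### The plan names two different stools for pre-treatment FLOTAC, and as the laboratory section is written only about 14 *T. trichiura* children per arm would have paired FLOTAC results, compared with Kato-Katz on unequal numbers of follow-up stools

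*Combined protocol and SAP*

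**What the plan says.** **Pre-treatment sample.** Three places point to the screening stool.
- Laboratory procedures, describing the baseline screening: "From 250 randomly selected stool samples 1-2 g will be preserved in SAF for subsequent examination with the FLOTAC method".
- Appendix 3, Week 2 to 5, before the trial lists are drawn up: "Preserve 1 g of stool in SAF from ~250 randomly selected children".
- Appendix 5, whose pre-treatment FLOTAC column is labelled "Sample A (FLOTAC"; Sample A is the stool examined before the trial yes/no entry.

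The Data analysis section differs. It lists the first stool with Kato-Katz alone ("Parasitological data of first stool examination (double Kato-Katz thick smear") and puts FLOTAC with the next one: "Parasitological data of second stool examination (double Kato-Katz thick smear and single FLOTAC". By order of collection this is the day-of-treatment stool.

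**Follow-up sample.** Laboratory procedures restricts repeat FLOTAC to stool "from those individuals examined with FLOTAC before treatment and who have been included in the trial". Appendix 3, Week 9 and 10, limits it to one stool per child ("Preserve 1 g of 1 stool sample in a labelled container"), and Appendix 5 has a single combined C/D column for it. Kato-Katz is done in duplicate on two follow-up stools from every trial child.

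**Planned use.** Data analysis: "The CR of the treatments and the ERR will be compared for each drug according to the results of either the Kato-Katz or the FLOTAC". A reading that joins both techniques is planned as well. Objective 3 asks how the methods perform both in parasitological surveys and in drug efficacy trials. The Sample size section covers only the CR comparison between treatments; it gives no number or precision for FLOTAC.

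**The concern.** There are three linked problems.

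First, the documents disagree on which stool supplies the FLOTAC baseline. The screening stool comes from weeks 2 to 5 and the treatment-day stool from weeks 5 and 6. The choice decides which egg count enters every FLOTAC-based CR and ERR, and whether Kato-Katz and FLOTAC are read on the same specimen.

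Second, the 250 are chosen without regard to infection, so only a minority can contribute to efficacy. Once these are split over four arms and reduced by the expected losses, few pairs remain for an analysis that the plan presents alongside the Kato-Katz one.

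Third, at follow-up Kato-Katz has two stools in which to find residual infection and FLOTAC has one. More stools find more infections, which lowers the apparent CR. A difference in CR between methods would therefore partly reflect sampling effort, and this bears on the efficacy-trial half of Objective 3.

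**Working it through.** **Inputs.** 250 FLOTAC samples (Laboratory procedures). Flowchart (Appendix 8): 1800 screened, 30% with *T. trichiura*, four arms of 135, losses of 7, 14 and 11 per arm. Other *T. trichiura* prevalences: 25% (Field procedures), 25.9% on one stool and 47.9% on three (Sample size), 42.9% (Study area). Assumed CRs: 20-45% for single drugs and 65-80% for combinations (Sample size).

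**Reproducing the plan's own figures.** 1800 × 0.30 = 540; 540/4 = 135; 135 − 7 − 14 = 114; 114 − 11 = 103. The sample size formula at 45% v 65% is 7.85 × (0.45 × 0.55 + 0.65 × 0.35)/0.20² + 2/0.20 + 2 = 105.2, which matches the stated 105. All of Table 1 reproduces.

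**Expected FLOTAC pairs per arm** = 250 × prevalence/4 × 103/135:

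| Prevalence | Infected among 250 | Pairs per arm |
|---|---|---|
| 25% | 62.5 | 11.9 |
| 25.9% | 64.75 | 12.4 |
| 30% | 75 | 14.3 |
| 42.9% | 107.25 | 20.5 |
| 47.9% | 119.75 | 22.8 |

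The last row is an upper bound, because 47.9% required three stools and screening uses one. At 30% the total over arms is 4 × 14.3 = 57 pairs. Chance alone would put a given arm between about 8 and 22.

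**Precision.** The 95% half-width at a CR of 65% is 1.96 × √(0.65 × 0.35/n):
- n = 12: 27 points
- n = 14: 25 points
- n = 23: 19.5 points
- n = 103: 9 points

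**Power between two arms at n = 14** (two-sided 5%, Fisher's exact test):

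| CRs compared | Power |
|---|---|
| 45% v 65% | 9% |
| 36% v 65% | 19% |
| 28% v 65% | 34% |
| 45% v 80% | 35% |
| 20% v 65% | 54% |
| 20% v 80% | 84% |

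With 103 per arm, power for 45% v 65% is 83% (normal approximation).

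**Number of stools.** The Sample size section reports 25.9% detected on one stool and 47.9% on three in the same schools with the same method. The number of stools alone therefore changes detection by a large amount.

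**Current FLOTAC workload.** Counting only *T. trichiura* children at follow-up gives 250 + 57 = 307 readings. Children with only *Ascaris* or hookworm are also randomised, so they too would be re-read. Assume independent infections at 30%, 22.5% and 16.5% (the last two from Study area). The share with any infection is 1 − 0.70 × 0.775 × 0.835 = 0.547. Then 250 × 0.547 × 0.85 × 0.90 = 105 repeats, or about 355 readings in all.

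**The case against.** The strongest reply is that the Data analysis sentence, read with Objective 3, more naturally describes a comparison of methods within each drug than of arms by FLOTAC. Such a comparison is paired and can be pooled over arms, giving about 57 pairs at 30% prevalence. This stands as a reading of the sentence, and it makes the power figures less central. It does not rescue the per-drug estimates, which still rest on about 14 children, and it makes the unequal number of stools more important.

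A reader might infer that FLOTAC could not separate any plausible pair of regimens. The documents do not support that. Table 1 needs only 12 per group for 20% v 80%. With the Zanzibar single-drug CR of 14.2% against the reported combination CR of 79.6%, exact power at 14 per arm is 92%. The shortfall covers much of the assumed range, including the plan's own design case, but not all of it.

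A reader might also infer that uninfected children in the 250 are wasted. They are not: they inform the survey half of Objective 3.

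Nor is the follow-up comparison beyond repair. Appendix 5 keeps Kato-Katz separately for Samples C and D, so a same-stool comparison is possible if the FLOTAC stool is identified.

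Finally, if the Data analysis list meant FLOTAC on the treatment-day stool of every trial child, the shortage would vanish. Laboratory procedures and Appendix 3 contradict this, which is itself a reason to reconcile them.

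**Conclusion.** The point holds in this form. The FLOTAC baseline stool is inconsistent between sections and must be settled. As Laboratory procedures is written, about 14 *T. trichiura* children per arm (12 to 23) would have paired FLOTAC results, so a per-drug CR near 65% would carry a half-width of about 20 to 27 points. Comparing CR between methods on one FLOTAC stool and two Kato-Katz stools mixes method with sampling effort.

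The counts rest on the flowchart's loss rates and on infection as defined by Kato-Katz. Children randomised for other species who prove FLOTAC-positive for *T. trichiura* would add some, but the documents give no figure. The power figures use CRs that the plan assumes for its Kato-Katz outcome. FLOTAC-based CRs may differ, since the Background describes FLOTAC as more sensitive.

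A reader might infer that the trial's main conclusions are at risk. They are not: the primary CR and ERR are defined on Kato-Katz.

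**What to change.** **Needed**
1. Reconcile Laboratory procedures, Data analysis, Appendix 3 (Week 2 to 5) and Appendix 5 on which pre-treatment stool is used for FLOTAC in trial children.
2. Record whether Sample C or D was used for follow-up FLOTAC. Base the Kato-Katz v FLOTAC comparison of CR and ERR on the same stools, pooled over arms as well as per drug, and report the two-stool Kato-Katz result separately.
3. State the expected number of pairs and the precision, and label FLOTAC-based efficacy by drug as exploratory.

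These cost a text correction, one extra recorded item and an analysis specification.

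**Optional.** Draw a larger share of the FLOTAC subsample from trial children, balanced over arms, on the day-of-treatment stool. Keep a random set of Kato-Katz-negative children, weighted by sampling fraction. This second set must use the screening stool, because children negative for all species are not asked for a treatment-day stool; a single sample for everyone is therefore not possible. The timetable allows it: the preserved samples are read in weeks 7 and 8, after treatment. As an example, 125 treated *T. trichiura* children with 10% lost at follow-up give 125 × 0.90/4 = 28 pairs per arm and ±18 points. That improves precision but does not give adequate power at the design case (22% exact for 45% v 65%). The cost is less precision for FLOTAC's extra yield in surveys. Any claim of equal workload should be set against about 355 current readings (if infections are independent), not 307.

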## Objectives

1. Efficacy and safety of albendazole and mebendazole alone and in combination with ivermectin against *T. trichiura*: We will carry out a randomized controlled trial in Kinyasini and Chaani school with the aim to compare the efficacy and safety of a single-dose treatment with albendazole (400 mg), and single-dose treatment with mebendazole (500 mg), a combination treatment with albendazole (400 mg oral dose) plus ivermectin ( 200 µg/kg oral dose) and a combination treatment with mebendazole (500 mg oral dose) plus ivermectin (200 µg/kg oral dose) against *T. trichiura.* Efficacy against other soil-transmitted helminth infections will also be determined to find out the most effective drug regimen to fight trichuriasis in particular and soil-transmitted helminthiasis in general. These results will guide policy recommendations in an appropriate way.

2. Development of resistance against albendazole/mebendazole after several years of mass-administration: To determine the current efficacy of a single-dose treatment with albendazole (400 mg single oral dose) or mebendazole (500 mg single oral dose) against *A. lumbricoides* and hookworm, to compare it to the efficacy of the drugs reported from Zanzibar in the 1990s and to shed light on a potential rise of drug resistance of *A. lumbricoides* and hookworm in Zanzibar within the above mentioned randomized controlled trial in Kinyasini and Chaani school.

3. Comparison of FLOTAC and Kato-Katz method: To compare the performance of the recently developed FLOTAC method with the Kato-Katz method applied by ‘default’ to diagnose soil-transmitted helminth infections under local conditions with the aim to determine their strengths and shortcomings in parasitological surveys and drug efficacy trials.

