**Week 7 and 8**

- Monitor and record side effects 3 days past treatment

- Examine the 250 SAF preserved stool samples with the FLOTAC method

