**Week 11 and 12**

- Examine the SAF preserved stool samples from the days of follow up with the FLOTAC method

Laboratory procedures:

Kato-Katz slide

- Prepare 2 Kato-Katz slides from every stool sample (baseline screening, day of treatment, days of follow up)

- Read for hookworm within 20-30 minutes (hookworm eggs clear fast). Other eggs can be read later. Magnification: 100x

- Keep slides for quality control

- Count all eggs, no estimation after partial reading

- Record result on form

- 10% of slides are re-read by senior technician for quality control

SAF conservation

- Label tube containing 10 ml SAF solution with ID

- Fill 1-2 g stool into the tube

- Mix well

FLOTAC

- Pass SAF preserved stool through an aperture with 350 µm in order to remove large fibres

- Add 10 ml of SAF to 1 g of stool

- Pipette this stool-SAF suspension into a 15 ml Falcon tube

- Centrifuge for 3 min at 170 g

- Discard supernatant

- Fill tube to the 6 ml mark with S4

- Mix pellet accurately and transfer 5 ml into one of the two chambers of the FLOTAC apparatus

- Record which sample was filled into which chamber of which apparatus

- Centrifuge apparatus for 5 min at 120 g

- Translate the top portion of the flotation chambers and remove rest of apparatus

- Read observation grids at a 100x magnification

- Record and count helminth eggs separately for each species

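### Masking of FLOTAC readers to Kato-Katz results is not specified, although FLOTAC is read later, in the same laboratory, from tubes carrying the child's ID

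*Combined protocol and SAP*

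**What the plan says.** **Aim.** Objective 3 is "To compare the performance of the recently developed FLOTAC method with the Kato-Katz method". The Data analysis section also compares cure rate (CR) and egg reduction rate (ERR) as measured by Kato-Katz, by FLOTAC, or by both combined.

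**Masking.** Laboratory procedures states: "All laboratory investigations will be blinded, e.g. the technicians examining the Kato-Katz slides or FLOTAC apparatus will not be aware of the treatment regimen". That technicians "will not be aware of the treatment regimen of the participants" is the only masking of laboratory readers described.

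**Readers.** The same section says that stool samples, all taken to the one laboratory, "will be examined by experienced laboratory technicians and the PhD-student". No separate FLOTAC readers are named. A 10% re-read is planned for Kato-Katz smears; none is stated for FLOTAC.

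**Order of work (Appendix 3).** In weeks 2 to 5 the instruction is "Prepare 2 Kato-Katz slides from each stool sample as described beyond". In weeks 5 and 6, lists are drawn up of the IDs of infected children. In weeks 7 and 8: "Examine the 250 SAF preserved stool samples with the FLOTAC method". Follow-up Kato-Katz is done in weeks 9 and 10, when children are also told their results. Follow-up FLOTAC is read in weeks 11 and 12.

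**Labels.** The SAF conservation step reads "Label tube containing 10 ml SAF solution with ID". No recoding step appears. The Kato-Katz form (Appendix 6) and the FLOTAC form (Appendix 7) are separate sheets, both keyed by ID.

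**The concern.** Masking to regimen protects comparisons between arms. It does nothing for a comparison between tests, and at baseline it is irrelevant, because the stools in the 250-sample comparison are collected before anyone is treated. What Objective 3 needs is that each test be read without knowledge of the other.

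The workflow makes the earlier result traceable: the tube carries the same identifier as the Kato-Katz record, and positive IDs have been listed before FLOTAC reading begins. A reader who knows, or looks up, that a child was Kato-Katz positive may search an empty grid for longer. A reader who knows the child was negative may accept a zero sooner or discount a doubtful egg. Estimated sensitivity and agreement would then partly reflect the earlier test. FLOTAC-based CR and ERR would be drawn towards the Kato-Katz answer, which weakens them as a separate check.

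**Working it through.** **1. Is FLOTAC always read second?** Taking differences of the week numbers in Appendix 3:

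| Stage | Kato-Katz | FLOTAC | Gap in weeks |
|---|---|---|---|
| Baseline | 2-5 | 7-8 | 7 − 5 = 2 to 8 − 2 = 6 |
| Follow-up | 9-10 | 11-12 | 11 − 10 = 1 to 12 − 9 = 3 |

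The documents disagree on which pre-treatment stool is used for FLOTAC. Laboratory procedures and Appendix 5 attach it to the baseline sample; Data analysis attaches it to the second one. Second-sample Kato-Katz falls in weeks 5-6, so FLOTAC is later on either reading.

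**2. Could a reader link a tube to a Kato-Katz result?** The label is the ID, the Kato-Katz form is keyed by ID, and the lists of infected children are lists of IDs. At follow-up only trial children contribute FLOTAC samples, so every tube is known by design to come from a child who was Kato-Katz positive for at least one species at baseline.

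**3. How large could the effect be?** There is no plan figure to reproduce: the Sample size section concerns cure rates only, and Objective 3 has no sample size or precision target. What follows is an illustration on assumed inputs.

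Let k and f be the true sensitivities of Kato-Katz and FLOTAC. Assume they are independent given infection, with no false positives, and take positive by either method as the reference. Among infected children:

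- positive by either method: R = 1 − (1 − k)(1 − f)
- masked apparent sensitivity: FLOTAC f/R, Kato-Katz k/R
- if a share s of the Kato-Katz-only positives is steered to FLOTAC positive, FLOTAC gains s·k(1 − f)/R
- if a share t of the FLOTAC-only positives is steered to negative, R falls to R′ = R − t(1 − k)f; FLOTAC becomes [f − t(1 − k)f]/R′ and Kato-Katz k/R′

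Prevalence cancels from these sensitivities. With s = 0.5 the FLOTAC gains are:

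- k = 0.5, f = 0.9: 0.5 × 0.5 × 0.1 / 0.95 = 2.6 points
- k = 0.6, f = 0.8: 0.5 × 0.6 × 0.2 / 0.92 = 6.5 points
- k = 0.7, f = 0.7: 0.5 × 0.7 × 0.3 / 0.91 = 11.5 points

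Kappa also needs a sample size and a prevalence. The table uses 250 samples and 25.9% infected (the 2007 single-stool figure in the Sample size section, used only for illustration).

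| k, f | FLOTAC: masked / s = 0.5 / t = 0.25 | Kato-Katz: masked / t = 0.25 | Kappa: masked / s = 0.5 / t = 0.25 |
|---|---|---|---|
| 0.5, 0.9 | 94.7 / 97.4 / 94.0% | 52.6 / 59.7% | 0.57 / 0.60 / 0.64 |
| 0.6, 0.8 | 87.0 / 93.5 / 85.7% | 65.2 / 71.4% | 0.62 / 0.68 / 0.67 |
| 0.7, 0.7 | 76.9 / 88.5 / 75.5% | 76.9 / 81.6% | 0.63 / 0.74 / 0.67 |

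Steering to positive flatters FLOTAC by about 3 to 12 points. Steering to negative lowers FLOTAC by about 1 point and raises Kato-Katz by about 5 to 7. Either way agreement is overstated, but the effect on FLOTAC's advantage changes sign.

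**The case against.** The strongest reply is that the blinding sentence is general. It covers all laboratory investigations and gives regimen as an example, so a reader might infer too much in saying that masking is confined to regimen. That stands: the fair statement is that masking between tests is not specified. But a general promise with no procedure behind it does not mask one test to the other, and labelling by ID works against it.

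A reader might also infer that FLOTAC readers will know the Kato-Katz results. The documents do not say so. Nobody is named as holding the infected-ID lists or the Appendix 5 sheet, and nothing says that one person reads both tests for the same child. The FLOTAC form has no Kato-Katz column. Unaided recall of about 250 tubes among some 2000 numbered children, weeks later, is unlikely. All this lowers the risk; it does not close the route, because results could be looked up by ID.

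Nor does Appendix 5 plainly disclose the earlier result. Its Kato-Katz columns may hold the number of smears rather than egg counts. Trial entry covers any of three species, while FLOTAC counts each species separately, and a child can be out of the trial because of illness, recent treatment or a missing second stool. At follow-up all tubes come from trial children, so trial status cannot separate them.

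Finally, the primary CR and ERR use Kato-Katz, which is read first and is untouched, and regimen masking limits any direct favouring of an arm in the FLOTAC-based rates. Both points are accepted.

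**Conclusion.** The gap is real and should be closed before FLOTAC reading starts. The plan does not specify that FLOTAC readers are masked to Kato-Katz results, and its sequence, shared pool of readers and ID labels leave an avoidable risk of review bias. The reach is Objective 3 and the FLOTAC-based CR and ERR. The risk is not a demonstrated bias, and neither its size nor its direction follows from the documents; the 3 to 12 points hold only under the assumed sensitivities and an assumed half of the readings steered one way.

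A reader might infer that a handful of changed readings would overturn a paired test of the two methods. The documents do not support that: they name no such test and give no discordant counts. With assumed counts of 15 FLOTAC-only against 6 Kato-Katz-only, exact McNemar gives p = 0.078, and 15 against 3 gives p = 0.0075. But if steering also removes some FLOTAC-only positives, 11 against 3 gives p = 0.057. With 25 FLOTAC-only positives against 5 to 11, the masked test is already significant (p = 0.0003 to 0.029). The reversal depends on the inputs chosen.

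**What to change.** 1. In Appendix 3 (SAF conservation and FLOTAC steps) and on the Appendix 7 form, replace the child ID with a random code, and use that code in the chamber log as well. An existing team member who does not read FLOTAC holds the key.
2. In Laboratory procedures, add that FLOTAC readers have no access to Kato-Katz results or to the lists of infected IDs until FLOTAC counts are entered, and that this applies at baseline and at follow-up.
3. Before codes are linked back to IDs, run a linkage check.

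The cost is one code list and a second set of labels for about 250 baseline tubes plus the follow-up tubes. No extra reading or staff is needed. The downside is a small risk of mislinked codes, which the linkage check limits. The change has to come before reading, because unmasked readings cannot be corrected at the analysis stage.
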